#### Graded activity

For this group, we will follow the protocols described by Macedo *et al.*[41] and Smeets *et al.*[42], which are based on individualized, progressive and sub-maximal exercises aiming to improve physical fitness and stimulate changes in behavior and attitudes due to pain. Positive reinforcement will be provided during the sessions (“you are doing great”, “congratulations”, “keep up with the good work”, “you can make it”), with the aim of maintaining the motivation.

In the beginning of the treatment, patients will select one or two activities considered difficult to them and receive guidance concerning them throughout the treatment, with the establishment of weekly goals. Participants will also receive an educational material (based on “Back Book”), with the purpose of providing important information about how to care for the spine. Weekly reading goals of the educational material will also be defined and the topics will be discussed at the end of each week. The protocol is described in Table 2.

**Table 2 T2:** Description of the protocol of the Graded Activity Group

**Exercise**	**Position**	**Sets/Duration**
Aerobic training on the treadmill	5-minute warm-up with speed of 5–8 km/h;	
	20-minute submaximal training at 70-80% maximum heart rate;	
	5-minute slow-down with gradual speed reduction.	
Lower limbs strengthening	Exercise for the quadriceps in sitting position;	3 sets of 12 repetitions for each limb
	Exercise for the hamstrings in standing position.	Intervals between series of 30 seconds
Trunk strengthening	Exercises for the erector spinae in ventral decubitus: trunk extension.	3 sets of 10 repetitions
		Intervals between series of 30 seconds

Heart rate (HR) will be calculated using the formula of Karvonen (maximum HR = 200 – age) for sedentary individuals: Exercise HR = Resting HR + 70% to 80% of maximum HR [43].

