## Methods and design

The study will be a randomised controlled trial comparing graded activity with a supervised exercise program in patients with non-specific cLBP. Each treatment program will consist of 12 individually supervised 1-hour sessions over a six-week period.

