#### Inclusion criteria

· Non-specific cLBP;

· Age between 18 and 65 years;

· A minimum pain intensity score of three in the 11-point Pain Numerical Rating Scale [24].

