#### Exclusion criteria

· Known or suspected serious spinal pathology (fractures, tumors, inflammatory or infective diseases of the spine);

· Nerve root compromise;

· Comorbid health conditions that would prevent active participation in the exercise programs;

· Pregnancy;

· Cardio-respiratory illnesses.

In order to ensure patients’ safe participation in the study, the *Physical Activity Readiness Questionnaire* (PAR-Q) will be used [30]. Those answering “yes” to any of the questions will be excluded.

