### Intervention

Interventions will last 60 minutes and will happen twice a week for 6 weeks. They will be supervised by the investigator and participants will be asked to report any complaint (adverse events) related or not to treatment. They will also be instructed not to initiate any intervention while during the study. Ongoing medications will be maintained.

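### The treadmill heart-rate formula for the graded activity arm contradicts Table 2 and, at an assumed resting rate of 55 bpm or more, puts the whole target above the plan's own maximum at every eligible age

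*Protocol article*

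**What the plan says.** The protocol article, under Graded activity, describes the programme as "individualized, progressive and sub-maximal exercises". Table 2 in that section sets the main treadmill block as "20-minute submaximal training at 70-80% maximum heart rate".

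The line directly below Table 2 attributes its calculation to a named heart-rate formula. It defines "maximum HR = 200 – age" and then gives "Exercise HR = Resting HR + 70% to 80% of maximum HR". Maximum heart rate is defined nowhere else, and no resting heart rate appears anywhere in the document.

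The Inclusion criteria set the age range: "Age between 18 and 65 years". Methods and design gives the exposure as "12 individually supervised 1-hour sessions over a six-week period".

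**The concern.** Table 2 and the line below it prescribe the intensity of the same treadmill block, and they disagree. Table 2 takes a percentage of maximum. The formula takes that same percentage and adds the whole resting rate, without first subtracting the resting rate from the maximum. At ordinary resting rates the result exceeds the maximum defined in the same sentence, so it cannot be submaximal.

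What is at stake is the dose in one of the two compared arms. A therapist who applies the formula as printed aims above the stated maximum. One who applies Table 2 aims lower by the full resting rate. One who repairs the formula by guesswork may reach a third target. The text does not say which is meant, so the treadmill component cannot be delivered uniformly or replicated from it.

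**Working it through.** **Inputs from the document.** Let M be maximum heart rate, 200 - age (line below Table 2). Ages run from 18 to 65 (Inclusion criteria), so M runs from 182 down to 135 bpm. The intensity is 70-80% in both places.

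**Assumed input.** Resting rate R is not given. I use 50 to 90 bpm.

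**Formulas.**

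- Table 2: 0.7M to 0.8M
- Printed line: R + 0.7M to R + 0.8M

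**Step 1: the contradiction, with no assumption about R.** Printed minus Table 2 equals R at both ends of the range, which is never zero. The two ranges stop overlapping once R + 0.7M > 0.8M, that is R > 0.1M: 18.2 bpm at age 18 and 13.5 at age 65.

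**Step 2: when the printed target exceeds the maximum.** The whole range is above M when R + 0.7M > M, that is R > 0.3M:

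- age 18: 0.3 x 182 = 54.6 bpm
- age 40: 0.3 x 160 = 48 bpm
- age 65: 0.3 x 135 = 40.5 bpm

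At R = 55 this holds at all 48 integer ages from 18 to 65. The margin is thin at age 18 (lower bound 55 + 127.4 = 182.4 against 182) and widens with age (149.5 against 135 at age 65). At R = 50 the whole range is above maximum at 32 of the 48 ages (34 and over). The top of the range is above maximum when R > 0.2M (36.4 bpm at age 18, 27 at age 65), so at R = 50 it is above at every age.

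**Step 3: size, in bpm (% of M in brackets).**

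| Age | M | Table 2 | Printed, R = 50 | Printed, R = 70 | Printed, R = 90 |
|---|---|---|---|---|---|
| 18 | 182 | 127.4-145.6 | 177.4-195.6 (97.5-107.5%) | 197.4-215.6 (108.5-118.5%) | 217.4-235.6 (119.5-129.5%) |
| 40 | 160 | 112-128 | 162-178 (101-111%) | 182-198 (114-124%) | 202-218 (126-136%) |
| 65 | 135 | 94.5-108 | 144.5-158 (107-117%) | 164.5-178 (122-132%) | 184.5-198 (137-147%) |

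**Step 4: sensitivity to the constant.** If the constant were 220 instead of 200 (an assumption, not in the document), the threshold at age 18 would be 0.3 x 202 = 60.6 bpm. The printed range would then lie above maximum at every age from R = 61.

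**Step 5: does the likely repair remove the conflict?** Suppose the line was meant as a heart-rate-reserve formula, R + 0.7(M - R) to R + 0.8(M - R). This is conjecture; the document does not print that form. It stays below M whenever R < M. At R = 70 it gives 148.4-159.6 at age 18, 133-142 at age 40 and 115.5-122 at age 65, about 82-90% of M. It exceeds Table 2 by 0.3R at the lower bound and 0.2R at the upper (21 and 14 bpm at R = 70). It has no overlap with Table 2 once R > M/3: 60.7 bpm at age 18, 53.3 at age 40 and 45 at age 65. Repairing the formula alone would leave two targets.

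**Exposure.** 12 sessions x 20 minutes = 240 minutes, out of 12 x 60 = 720.

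**The case against.** The strongest reply is that the text excludes the supra-maximal reading by itself. Table 2 together with the stated maximum gives a complete, workable target (112-128 bpm at age 40), and the programme is called submaximal twice. A supervisor who computed 182-198 against a maximum of 160 would recognise a slip. Sessions are watched ("They will be supervised by the investigator"), and the exclusions cover "Cardio-respiratory illnesses" and any positive answer on the readiness questionnaire. This is also a condensed article that cites its sources for the method, so staff may well have worked from a correct rule.

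Much of this stands. Literal delivery of the printed target is unlikely, the exclusions and supervision lower the safety risk, and Table 2 alone does give a deliverable dose. It is also fair that the resting rate is assumed and that the reserve form is not in the document.

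None of it settles which rule applies. Condensing an article excuses omissions, not a formula stated wrongly. Table 2 needs the maximum defined in the faulty line, so a reader has to use that line. The safeguards do not tell the supervisor which number to set. Once the supra-maximal reading is ruled out, the choice between a percentage of maximum and a target adjusted for resting rate remains open, and at R = 70 it is worth 14-21 bpm.

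**Conclusion.** The formula is wrong as written. That it contradicts Table 2 follows from the document alone. That its whole range exceeds the plan's maximum at every eligible age rests on one assumption, a resting rate of at least 55 bpm; at 50 bpm the claim holds from age 34 up. At an assumed 70 bpm the printed target is about 108-132% of maximum across ages 18 to 65, against 70-80% in Table 2.

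The consequence is local: the intensity of one third of session time in one arm is not fixed, with a residual safety concern if anyone follows the line literally. The rest of the arm, the sample size and the analysis are untouched. It should be corrected before treatment starts.

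**What to change.** Keep one rule and make the line and Table 2 agree.

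- **Option A:** remove the resting-rate term so that the target is 70-80% x (200 - age). Table 2 stays as it is. Drop the attribution to the named formula as well, because the document ties the resting-rate term to it. At age 40 the target is 112-128 bpm.
- **Option B:** write the target as resting rate + 70-80% x (maximum - resting rate), and change the Table 2 entry to 70-80% of heart-rate reserve. At age 40 and an assumed resting rate of 70 the target is 133-142 bpm.

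Both stay below the plan's maximum. The choice is clinical: the responsible clinicians should make it explicitly and confirm the constant 200 at the same time, since every target depends on it.

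Option A costs an edit to one line. Option B costs one line, one table cell and a resting heart rate for each patient in the arm. Either way the person supervising the sessions must be told. Neither option needs more patients or visits.

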### Sample size calculation

Sample size was defined in order to detect a 2-point difference between groups on the pain intensity outcome measured by the *Pain Numerical Rating Scale*, assuming a standard deviation of 1.9 points [24]. We also sought power to detect a 4-point difference in functional disability measured by the *Roland Morris Disability Questionnaire*, with an estimated standard deviation of 4.9 points [24,25,36]. Power was defined as 80% for an alpha of 5% and attrition (drop-outs) of 15%. Accordingly, 33 participants per group will be needed.

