### Procedures

All measurements will be conducted by a physical therapist blinded to patients’ groups. The investigator will confirm the eligibility criteria, as well as obtain demographic (civil status, education, tabagism and use of medication) and anthropometric data (age, height, weight and body mass index). Past treatments and use of medication for cLBP will also be recorded. The investigator will also assess primary (pain severity and functional disability) and secondary outcomes (quality of life, global perceived effect, return to work, physical activity, physical capacity and kinesiophobia). Patients will be assessed at baseline, immediately after the treatment and at three and six-month follow-up.

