### Statistical analyses

All of the statistical analysis will be based on intention-to-treat basis [44]. We will use linear mixed models to test for treatment effects between groups at the end of the treatment and at three and six-month follow-up. Treatment effect sizes will be calculated for each time points, as well as statistical significance. Analyses will be conducted using SPSS 19 and SigmaPlot 10. A level of significance of 5% will be used.

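### The stated sample-size inputs give 30 per group, not 33; with 33 per group and 15% loss the power is about 85% for disability and 97% for pain

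*Protocol article*

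**What the plan says.** The section Sample size calculation of the protocol article gives two targets. The first is pain on the numerical rating scale: "Sample size was defined in order to detect a 2-point difference between groups on the pain intensity outcome", "assuming a standard deviation of 1.9 points". The second is the Roland Morris questionnaire: "We also sought power to detect a 4-point difference in functional disability", "with an estimated standard deviation of 4.9 points". The design parameters follow: "Power was defined as 80% for an alpha of 5% and attrition (drop-outs) of 15" (per cent). The conclusion is drawn directly from these: "Accordingly, 33 participants per group will be needed". The Abstract and the section on enrolment carry the resulting total of 66.

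Both targets are primary outcomes. Under Procedures: "The investigator will also assess primary (pain severity and functional disability) and secondary outcomes". The Statistical analyses section adds only "A level of significance of 5% will be used". The article does not state sidedness, a division of alpha between the two outcomes, a joint-power target or a rounding allowance.

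**The concern.** The sentence giving 33 presents it as the consequence of the inputs just listed. Every input that a comparison of two means needs is there, apart from sidedness and the choice between the t and normal calculation, so a reader should be able to reproduce the figure. If it cannot be reproduced, either the power or attrition on the page is not what was used, or an allowance was left out. The reader cannot tell which.

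What is at stake is the accuracy of the power statement, which will be carried into the results paper and into any ethics or journal reporting. As written, it understates the power of the design on both primary outcomes. It does not put the trial's ability to detect its planned differences in doubt.

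**Working it through.** **Inputs** (all from Sample size calculation): pain difference 2, SD 1.9; Roland Morris difference 4, SD 4.9; power 80%; alpha 5%; attrition 15%; two equal groups. Assumptions: two-sided test, two-sample comparison of means.

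**Standardised differences.** Pain: 2/1.9 = 1.053. Disability: 4/4.9 = 0.816. Disability is the smaller, so it determines the size.

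**Step 1: try to reproduce 33 from the stated inputs.** The normal approximation is n = 2(1.960 + 0.842)² × (SD/difference)² per group.

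- Disability: 2 × 7.85 × (4.9/4)² = 15.70 × 1.501 = 23.6, so 24 evaluable; 24/0.85 = 28.2, so 29 recruited.
- Pain: 15.70 × (1.9/2)² = 15.70 × 0.9025 = 14.2, so 15 evaluable; 15/0.85 = 17.6, so 18 recruited.

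The t-test calculation, which allows for estimating the SD, gives slightly more:

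- Disability: n = 24.55, so 25 evaluable; 25/0.85 = 29.4, so **30 recruited**.
- Pain: n = 15.19, so 16 evaluable; 16/0.85 = 18.8, so **19 recruited**.

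The other readings of the same inputs, for disability:

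| Reading | Evaluable | Recruited per group |
|---|---|---|
| t-test, two-sided, n/0.85 | 25 | 30 |
| t-test, two-sided, n × 1.15 | 25 | 29 |
| Normal, two-sided, n/0.85 | 24 | 29 |
| Normal, two-sided, n × 1.15 | 24 | 28 |
| t-test, one-sided 5%, n/0.85 | 20 | 24 |

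The largest is 30. None gives 33. The gap is at least 3 per group, or 66 against 60 in total (10%), which is more than rounding.

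**Step 2: which unstated inputs reach 33 or come near it?** All for disability by t-test at two-sided 5%, unless noted.

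| Unstated input | Evaluable | Recruited per group |
|---|---|---|
| 85% power, 15% attrition | 27.94 → 28 | 28/0.85 = 32.9 → 33 |
| 90% power, no attrition | 32.53 → 33 | 33 |
| 80% joint power for both outcomes, treated as independent | 27 (joint power 0.81) | 27/0.85 = 31.8 → 32 |
| 80% power at alpha 0.025 per outcome | 29.82 → 30 | 30/0.85 = 35.3 → 36 |

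Two different inputs give exactly 33 and a third gives 32, so the source of the figure cannot be identified from the article.

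**Step 3: power of the design as it stands.** 33 × 0.85 = 28.05, so about 28 evaluable per group. The noncentrality is the standardised difference × √(n/2), with √14 = 3.742.

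- Disability: 0.816 × 3.742 = 3.05; t-test power **85.1%** (normal approximation 86.3%).
- Pain: 1.053 × 3.742 = 3.94; t-test power **97.2%** (normal approximation 97.6%).

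**Step 4: how much margin is there?** Disability needs 25 evaluable, so 80% power is kept up to a loss of 1 − 25/33 = 24%. At alpha 0.025 per outcome, 28 evaluable per group gives 77.1% power for disability and 94.6% for pain.

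**The case against.** The strongest reply is that nothing is wrong in substance. Eighty per cent can be read as a target to be met, and 33 per group meets it for both outcomes after the planned loss. The trial has more power than claimed, no recruitment decision changes, and a null result will be read mainly from its confidence interval. This stands, and it is why the point is minor. It does not remove the inconsistency, because the text presents 33 as what the inputs require.

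A second reply is that a journal article condenses the full calculation. That would answer a complaint about missing detail. Here the article prints both the inputs and the result, and they disagree.

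Three stronger readings are tempting, and the document supports none of them.

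- A reader might infer that the sample size is wrong and should change. The discrepancy is in the safe direction, and nothing in it argues for recruiting fewer or more than 66.
- A reader might infer that 85% power was used, since it gives exactly 33. So does 90% power without attrition, and a joint-power target for both outcomes gives about 32. The article does not say which, if any, applied.
- A reader might infer that the spare patients pay for a multiplicity correction on the two primary outcomes. Under a Bonferroni split they do not: disability falls to 77.1% power, and 80% would need 36 per group. A stepwise Holm procedure would lose less. Treating the outcomes as independent, disability power is 0.771 + (0.851 − 0.771) × 0.946 = about 0.85, but only if the planned pain effect is real as well. The article names no correction, so no such cover can be claimed.

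**Conclusion.** The concern holds as a reporting error of low consequence. The stated power, attrition and effect sizes do not belong with the stated 33 per group. They give at most 30, and the design as stated has about 85% power for disability and 97% for pain, not 80%.

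This rests on a simple comparison of two group means, a two-sided 5% test and the article's own SDs. The finding does not depend on sidedness, on t against normal, or on how attrition is applied, since every alternative moves further below 33. The planned analysis is a linear mixed model, but the article states no correlation or repeated-measures allowance that could be used to reach 33.

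**What to change.** Keep 66 patients. Replace the closing sentences of Sample size calculation with a statement that follows from the inputs, along these lines: *33 per group, about 28 evaluable after 15% attrition, gives about 85% power for a 4-point Roland Morris difference and about 97% for a 2-point pain difference, at a two-sided 5% level.* If a different power, attrition, SD, alpha or joint-power target actually produced 33, state that input instead. The sponsor should check which it was before choosing the wording.

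Do not add a claim that the margin covers a multiplicity correction. If alpha is to be divided between the two primary outcomes, name the procedure and recompute the power for it.

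The cost is one sentence, with no change to enrolment, conduct or analysis.

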### Statistical analyses

All of the statistical analysis will be based on intention-to-treat basis [44]. We will use linear mixed models to test for treatment effects between groups at the end of the treatment and at three and six-month follow-up. Treatment effect sizes will be calculated for each time points, as well as statistical significance. Analyses will be conducted using SPSS 19 and SigmaPlot 10. A level of significance of 5% will be used.

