### Primary outcomes

#### Pain

Pain will be assessed quantitatively and qualitatively with the *Numerical Rating Scale* (NRS) and the *McGill Pain Questionnaire*. The NRS is an 11-point scale ranging from 0 to 10, in which 0 defines absence of pain and 10 describes unbearable pain [24]. Participants will be asked to rate the average pain levels over the week before assessment [24].

The *McGill Pain Questionnaire* provides a multidimensional assessment of pain. It consists of 78 descriptors of the quantity and quality of pain which are grouped in four major domains (sensory, affective, evaluative and miscellanea) and 20 sub-domains with 1 to 5 descriptors each, to which intensity values are assigned. The questionnaire is used to describe pain experience and the score corresponds to the sum of the aggregated values. Maximal scores will be: Sensorial = 41, Affective = 14, Evaluative = 5, Miscellanea = 17, Total = 7 [35].

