#### Functional disability

The *Roland Morris Disability Questionnaire* will be used to assess functional disability due to LBP. It consists of 24 questions focusing on normal activities of daily life. Each affirmative answer corresponds to 1 point and the final score is determined by the total number of points. Total score ranges from 0 to 24 and higher scores reflect increased disability. Scores above 14 reflect severe impairment [24,25,36].

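### Two primary outcomes (plus the McGill under the primary heading) are tested at three visits at 5% with no primary visit or ordering, so the chance of a false primary result is about 18–32% under assumed correlations if any one result counts

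*Protocol article*

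**What the plan says.** **Primary outcomes.** The Procedures section names two constructs: "The investigator will also assess primary (pain severity and functional disability) and secondary outcomes". Under the heading Primary outcomes, the Pain subsection has two instruments: "Pain will be assessed quantitatively and qualitatively with the" 0–10 numerical rating scale and the McGill questionnaire. The Functional disability subsection has one: "The *Roland Morris Disability Questionnaire* will be used to assess functional disability due to LBP".

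**Analysis.** The Statistical analyses section uses linear mixed models to compare the groups at end of treatment, three months and six months. It adds: "Treatment effect sizes will be calculated for each time points, as well as statistical significance". On the level it says only: "A level of significance of 5% will be used".

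**Sample size.** The Sample size calculation section plans for a 2-point difference on the rating scale (SD 1.9). It continues: "We also sought power to detect a 4-point difference in functional disability" (SD 4.9). It then states: "Power was defined as 80% for an alpha of 5% and attrition (drop-outs) of 15" per cent, giving 33 per group. It names no visit and plans no difference for the McGill.

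The article nowhere names a primary visit, ranks the primary outcomes, divides the 5%, or says what pattern of results would show that the programmes differ.

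**The concern.** The sample size treats each of two outcomes as one comparison at 5%. The analysis produces six primary comparisons (two outcomes, three visits), or nine if the McGill total is counted, and attaches significance to each. Nothing marks one of them as the confirmatory comparison.

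The Discussion says the trial should provide evidence to guide treatment decisions. If the result is significant on one scale at one visit only, a reader cannot tell whether that was the planned test or the most favourable of several. The nominal 5% would not describe the risk of a false finding. The primary outcome and visit belong in the protocol because the sample size depends on them, and they cannot be credibly chosen once results are known.

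**Working it through.** **1. The plan's own figure.** For two means, n per group = 2(z₀.₉₇₅ + z₀.₈₀)²/d², with (1.960 + 0.842)² = 7.849.
- Rating scale: d = 2/1.9 = 1.053, so n = 15.698/1.108 = 14.2, rounded up to 15; 15/0.85 = 17.6, so 18 per group.
- Roland Morris: d = 4/4.9 = 0.816, so n = 15.698/0.666 = 23.6, rounded up to 24; 24/0.85 = 28.2, so 29 per group (t-based: 25, then 30).

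The stated 33 is not reproduced, but it errs on the large side, and this point does not depend on it. Completers: 33 × 0.85 = 28 per arm.

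**2. Error rate with independent tests.** The chance of at least one false positive among k tests is 1 − 0.95^k.
- k = 6: 26.5%.
- k = 9: 37.0%.

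**3. Error rate with correlated tests.** The tests share patients, so independence overstates the rate. I simulated multivariate normal test statistics with no true effect and counted a false claim when any |Z| exceeded 1.96. The correlation between two different scales at two different visits was taken as the between-scale value times the between-visit value. All correlations are assumptions.

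| Between scales | Between visits | 2 outcomes × 3 visits | 3 instruments × 3 visits |
|---|---|---|---|
| 0.3 | 0.5 | 23% | 32% |
| 0.5 | 0.5 | 22% | 29% |
| 0.7 | 0.7 | 18% | 23% |
| 0.9 | 0.9 | 11–12% | 14% |

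One outcome alone over three visits gives 10.8% at a between-visit correlation of 0.7. Two outcomes at a single visit, each at 5%, give 8–10% for between-scale correlations of 0.3–0.7. Both the visits and the outcomes therefore contribute.

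**4. Power under the proposed rule.** Hochberg for two endpoints: reject both if both p-values are below 0.05; otherwise reject the smaller if it is below 0.025. Inputs: 28 per arm, d = 1.053 and 0.816, between-scale correlation 0.3–0.7, t-based.
- Both planned effects real: about 96% (pain) and 85% (disability).
- Only disability differs: pain is then rarely significant, so disability is in effect tested at 2.5%. Power is about 77% (79% by normal approximation), below the planned 80%.
- To restore 80% at the 2.5% level for disability, the normal formula needs 29 completers, or 29/0.85 = 34.1, so 35 per group. The t-based figures are 30 completers and 36 per group.

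**The case against.** **Detail may sit elsewhere.** The article condenses a fuller protocol, and a multiplicity procedure or success rule is often left to the SAP. The 5% sentence does not say whether it applies per test or overall. This is fair, and the absence of a named procedure would not be a finding by itself. What stands is what the article does fix: more than one primary outcome, significance at each of three visits, one flat level, and a sample size that names no visit.

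**The rates need a success rule that the text does not state.** A reader might infer that the plan intends to declare superiority on the best result. It does not say so; it only reports effects and significance by visit. If both outcomes had to succeed at one fixed visit, there would be no inflation. The rates are therefore conditional on an any-one-counts reading, which the text neither adopts nor excludes.

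**The McGill may not be a co-equal primary test.** The Procedures section speaks of pain severity, and the sample size rests on the rating scale alone. The two-outcome range is therefore the better supported. The nine-test range applies only if the placement under Primary outcomes is taken at face value.

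**A larger count is not supported.** A reader might also count each McGill domain as a separate primary test. The Pain subsection lists domain maxima but never promises a test per domain. The total is also the sum of its parts and could not be treated as a separate scale.

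**Conclusion.** The concern holds in this form: the article sets several primary comparisons at a flat 5% and identifies none as confirmatory. If any one significant primary result is taken as showing a difference, the familywise error is about 18–23% for the two powered outcomes at three visits, and about 23–32% with the McGill total added. Both ranges rest on assumed correlations of 0.3–0.7 between scales and 0.5–0.7 between visits. Correlations of 0.9 throughout lower them to about 11–14%, still more than twice the nominal level. The documents do not support saying that the trial will claim success on any single result, or that the McGill domains are each tested.

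**What to change.** Before unblinded data are seen:
- The investigators name one primary visit. The choice is theirs: the document gives one overall attrition figure and none by visit, so expected dropout does not settle it.
- The numerical rating scale and the Roland Morris at that visit are the two primary endpoints, tested by Hochberg or Holm at an overall two-sided 5%.
- The McGill and the other visits become secondary, reported as estimates with 95% intervals.

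Suggested text: *The primary endpoints are the pain numerical rating scale and the Roland Morris score at [visit]. They are tested with the Hochberg procedure at an overall two-sided 5% level. All other scales and visits are secondary and are reported as estimates with 95% confidence intervals.*

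**Cost.** A lone significant result on the McGill or at another visit is no longer confirmatory. The planned 66 patients suffice if both effects are as assumed. The protocol should also state that disability power falls to about 77% if only disability differs.
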